### Other study parameters

Peroperative blood loss (continue), blood transfusions either autologous or homologous (categorical), other blood product administration (categorical), total operative time (continue), clamping time (continue), use of adjunctive hemostatic products (categorical), length of hospital (including ICU) stay (continue), and health status (categorical and continue); ACT values measured (continue); the amount of heparin and protamine used (categorical). The outcomes of the first 5 patients from all participating hospitals will be analyzed and compared with the outcomes of patients included later. Data on the previous heparin protocol will be collected per hospital. Analyses will be conducted to determine whether the previously used heparin protocol affects the outcomes.

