### Main study parameter/endpoint safety {12}

Incidence of bleeding complications according to E-CABG classification, grade 1 and higher: per- or postoperative transfusion of 2 or more units of red blood cells, transfusion of platelets, transfusion of fresh frozen plasma, or re-operation for bleeding during the hospital stay [30, 31]. For the bleeding complications, a non-inferiority test will be used. This will be tested using a one-sided *t* test with an alpha of 0.025.

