### Secondary study parameters/endpoints {12}

Secondary endpoints: complications (non-TEC), within 30 days postoperative or in the same admission, as defined by DSAA and suggested standards for reports on aneurysmal disease: all complications requiring re-operation, longer hospital stay, and all other complications; incidence of kidney injury as defined by RIFLE criteria: rise of serum creatinine > 100% or decrease of eGFR with 50% [35]; allergic reactions; ACT values (in the intervention group), total heparin administration, and protamine administration; peroperative blood loss, blood transfusions either autologous or homologous, other blood product administration, total operative time, aortic clamping time, use of adjunctive hemostatic products, and length of hospital (including ICU) stay; health status as measured with the EQ-5D-5L; and economic and health care cost evaluation by IMCQ and IPCQ and addition of out-of-pocket expenses.

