### Secondary study parameter(s)

Secondary endpoints include all complications as defined by DSAA and suggested standards for reports on aneurysmal disease. Health status was measured with the EQ-5D-5L questionnaire. Differences in categorical outcomes between the intervention and control groups will be expressed as the absolute risk difference with a 95% confidence interval. Differences in continuous outcomes will be tested with Student’s *t*-test in case of a normal distribution or the Mann-Whitney *U*-test in case the data do not follow the normal distribution. The level of significance is set at a two-sided *P*-value < 0.05.

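### The amounts of heparin and protamine are labelled categorical, so their comparison becomes a risk difference that cannot express dose; units transfused would usefully supplement the yes/no comparison

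*Protocol article*

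**What the plan says.** The section Secondary study parameters/endpoints {12} lists among the secondary endpoints "total heparin administration, and protamine administration; peroperative blood loss, blood transfusions either autologous or homologous, other blood product administration". The later section Other study parameters assigns a type to each variable. Blood loss is continuous ("Peroperative blood loss (continue"), as are operative time, clamping time and ACT values. Transfusion variables are categorical: "blood transfusions either autologous or homologous (categorical), other blood product administration (categorical". So are the drug amounts: "the amount of heparin and protamine used (categorical".

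The analysis rule stands in the section just before, Secondary study parameter(s): "Differences in categorical outcomes between the intervention and control groups will be expressed as the absolute risk difference with a 95% confidence interval". For the other type it says "Differences in continuous outcomes will be tested with Student’s *t*-test in case of a normal distribution or the Mann-Whitney *U*-test" when the data are not normal.

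The formal bleeding comparison is separate. The primary safety endpoint is E-CABG grade 1 or higher, met by "per- or postoperative transfusion of 2 or more units of red blood cells", by any platelet or fresh frozen plasma transfusion, or by re-operation for bleeding.

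**The concern.** For heparin and protamine the label does not fit the variable. The endpoint list speaks of total heparin administered, doses are prescribed numerically, and the text offers no bands. A single risk difference needs a cut, and none is given. Total heparin is the direct measure of how different the two treatments were in practice. That matters here because extra heparin is permitted in the control arm on stated indications, and the Discussion expects some deviation in both arms.

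For transfusions and blood products the label is defensible, but it yields little that is new. Any platelet or plasma transfusion already meets grade 1, so yes/no for those products is a component of the primary safety endpoint. Yes/no for red cells mainly moves the cut from 2 units to 1. What a reader would still want is how much more blood, if any, the intervention costs per patient. A risk difference cannot supply that.

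**Working it through.** **1. The plan's own figures.** No sample size or power is stated for these variables. The stated sizes reproduce but belong to other endpoints.
- Efficacy, 19% against 11%, two-sided 5%, 80% power: uncorrected n = [1.96√(2×0.15×0.85) + 0.842√(0.19×0.81 + 0.11×0.89)]² / 0.08² = 312. With the continuity correction, (312/4)(1 + √(1 + 4/(312×0.08)))² = 337 per arm. Then 674/0.9 = 749, stated as 750.
- Bleeding, 32% against 33%, margin 11 points, one-sided 5%: (0.32×0.68 + 0.33×0.67)(1.645 + 0.842)² / 0.10² = 272 per arm.

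**2. Heparin: what a risk difference would show.** Take an assumed weight of 85 kg (SD 15); the article gives none. The control dose is 5,000 IU, or 5,000/85 = 58.8 IU/kg. The starting dose in the ACT arm is 100 × 85 = 8,500 IU. The difference is 3,500 IU, or 41.2 IU/kg. If every ACT patient also had one further 60 IU/kg dose, the total would be 160 × 85 = 13,600 IU and the difference 8,600 IU. Now cut at more than 5,000 IU, with no extra doses in controls. The share above the cut in the ACT arm is P(weight > 50 kg) = Φ(35/15) = 99% in the first case and practically 100% in the second. The risk difference moves from 99 to about 100 points while the dose difference more than doubles. The loss is in the estimate, not in power, because the arms differ by design.

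**3. Transfusion: possible power gain.** The article gives neither a distribution of units nor a rate of 2 or more red-cell units. Its 32% is composite grade 1 or higher bleeding, so using 32% for the 2-unit cut is an assumption. Power of the cut (375 per arm, two-sided 5%) is approximately Φ[(Δ − 1.96 SE)/SE], with SE = √(2p̄(1−p̄)/375):
- 33%: SE 0.0342, power about 6% with both tails counted.
- 36%: SE 0.0346, (0.04 − 0.0678)/0.0346 = −0.80, power about 21%.
- 40%: SE 0.0351, (0.08 − 0.0687)/0.0351 = 0.32, power about 63%.

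Simulated negative binomial units (dispersion 0.3 to 2; 337 and 375 per arm; 2,000 trials per setting) give these gains for Mann-Whitney on units over the 2-unit cut: essentially none at 33%, about 2 to 6 points at 36%, and about 7 to 14 points at 40%.

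Other assumed patterns at 337 per arm (2,000 trials each) gave this power:

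| Pattern | Any unit | 2 or more | Mann-Whitney | t test on units |
|---|---|---|---|---|
| Negative binomial, k = 0.4, mean 1.3 vs 1.8 | 30% | 40% | 47% | 66% |
| Negative binomial, k = 1, mean 1.3 vs 1.8 | 55% | 71% | 81% | 90% |
| Only share transfused differs, 40% vs 50% | 75% | 42% | 71% | 46% |
| Only units among the transfused differ | 5% | 28% | 14% | 68% |
| Both differ modestly | 36% | 50% | 53% | 70% |

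**4. What the amount adds as an estimate.** With k = 1, P(2 or more) = (μ/(1+μ))². Then 0.32 gives μ = 1.30, 0.33 gives 1.35 and 0.40 gives 1.72. The same data would be reported as 0.05 or 0.42 extra units per patient, which the proportions do not convey.

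**The case against.** A reader might infer that all the labelled variables are amounts and that the plan throws away power on its key bleeding secondaries. The documents do not support that.
- For blood the text speaks of transfusions and administration, not of units. Received yes/no, or by type, is a proper categorical variable. Only the heparin and protamine item names an amount.
- Nothing ranks these secondaries as key and none is powered. Formal bleeding inference rests on the E-CABG endpoint, and blood loss stays continuous.
- Heparin amount is an exposure measure, so lost power there is of little consequence.
- The favourable power scenario is far from the plan's expectation of 33% against 32%. At 40%, with the 2-unit cut standing in for grade 1 or higher, the non-inferiority test at one-sided 2.5% would succeed with probability about Φ[(0.11 − 0.08)/0.0349 − 1.96] = 14% with 375 per arm. The primary safety test would then usually already have failed to support the claim of no excess bleeding.
- The rank test can lose: 71% against 75% for yes/no if only the share transfused changes, and 14% against 28% for the 2-unit cut if only units among the transfused change.

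All of this stands, and it confines the transfusion part to a supplement. It does not touch the heparin and protamine label. One could add that an analysis plan not shown may recode these variables. But the article does more than omit detail: it states a type for each and a rule for that type.

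**Conclusion.** For heparin and protamine, the stated label is wrong for the variable and leads to a summary that cannot show the dose difference between arms. This rests on the text alone, plus the reading that the rule for categorical outcomes applies because total heparin and protamine are listed as secondary endpoints.

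For transfusions and blood products, the categorical comparison is valid and should stay. Its limitation is that it largely repeats parts of the primary safety endpoint, so units per patient are a worthwhile addition. A general loss of power should not be claimed. Under assumed negative binomial units the gain over the 2-unit cut runs from none at 33% to about 7 to 14 points at 40%, and it reverses in some patterns. The 32% starting point is borrowed from a composite rate.

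Severity is minor. No primary conclusion of the trial depends on this point.

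**What to change.** In Other study parameters:
- Relabel total heparin (IU and IU/kg) and protamine amount as continuous. Report the between-arm difference with the t test or Mann-Whitney test that the plan already names, giving the mean difference with a 95% confidence interval so that separation can be read in dose units.
- Keep transfusion and blood product administration as yes/no with the risk difference. Add the number of units per patient (volume for autologous blood), with the mean difference, a bootstrap 95% interval and a Mann-Whitney test, marked as supplementary.
- Leave the E-CABG grade 1 or higher endpoint and its non-inferiority test unchanged.

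The cost is a wording change and a little more analysis. Red-cell units are already needed for the E-CABG thresholds of 2 and 5 units, and numeric heparin and protamine doses for the per-protocol rule on deviations above 50%. The bootstrap is already used in the economic evaluation. Whether the case report form holds platelet and plasma counts and autologous volume should be checked, since grade 1 needs only the fact of a platelet or plasma transfusion. The downside is a few more secondary comparisons without multiplicity adjustment, and a rank test that is sometimes weaker than the proportion it accompanies. Both are reasons to keep the proportion in the report.

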## Economic evaluation

### Cost-effectiveness analysis (CEA)

General considerations: We hypothesize that ACT-guided heparinization could lower the rate of TEC and TEC-related mortality to in total 11% and that the quality of life can be increased from 73 to 76%. The economic evaluation of ACT-guided heparinization against standard care with a standardized bolus of heparin will be performed as cost-utility analyses and a cost-effectiveness analysis from a societal perspective with the costs per quality-adjusted life year (QALY) and the costs per prevented complication as the primary economic outcomes. The cost-utility analysis can be used for policy making and composition of a guideline. The cost-effectiveness analysis (CEA) relates to the clinical outcome parameter and may be used for prioritization or benchmarking of strategies that enhance surgical patient safety. The CEA and CUA will be based on a time horizon of 6 months. All related complications are within the time horizon of 6 months and patients will be recovered from the surgery. For on-going complications such as leg amputations, colostomy, permanent neurological deficits, and dialysis, a CEA and CUA with a lifelong time horizon will be made using extrapolation and model-based techniques. For this time horizon, discounting of effects and costs will be performed as stated in the most recent guidelines for cost analysis [36]. To account for uncertainties in the lifelong time horizon, a probabilistic sensitivity analysis will be performed.

Incremental cost-effectiveness ratios will be calculated as the difference in costs per QALY gained and as the difference in costs prevented complications. Sampling variability will be accounted for by bias-corrected and accelerated non-parametric bootstrapping. Results will be reported along with their 95% confidence intervals and displayed graphically with cost-effectiveness planes and with cost-effectiveness acceptability curves. One-way and multi-way sensitivity analyses will be done for the unit costs of the most common complications. Some missing data can be expected; if missing data is at random, this will be handled through multiple imputations with predictive mean matching.

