**Discussion:**

The ACTION-1 trial is an international RCT during open AAA surgery, designed to show superiority of ACT-guided heparinization compared to the current standard of a single bolus of 5000 IU of heparin. A significant reduction in TEC and mortality, without more major bleeding complications, must be proven with a relevant economic benefit.

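### The planned bootstrap 95% interval for the cost-effectiveness ratio is not interpretable once replicates leave the dearer-and-better quadrant, which the small expected QALY gain makes likely unless ACT-guided care is clearly dearer

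*Protocol article*

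**What the plan says.** The section on the cost-effectiveness analysis takes "costs per quality-adjusted life year (QALY) and the costs per prevented complication as the primary economic outcomes". Both are ratios. It continues:

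- Estimator: "Incremental cost-effectiveness ratios will be calculated as the difference in costs per QALY gained", with a second ratio for prevented complications.
- Uncertainty: "Sampling variability will be accounted for by bias-corrected and accelerated non-parametric bootstrapping. Results will be reported along with their 95% confidence intervals".
- Reporting, with that last sentence in full: "Results will be reported along with their 95% confidence intervals and displayed graphically with cost-effectiveness planes and with cost-effectiveness acceptability curves".
- Horizon: "The CEA and CUA will be based on a time horizon of 6 months", with lifelong modelling added for lasting complications.
- Expected effect: "that the quality of life can be increased from 73 to 76" per cent.

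No cost difference, cost SD or QALY SD is given. The nearest text is in the Discussion part of the abstract, where the clinical result "must be proven with a relevant economic benefit", and in the study objectives, which expect fewer re-operations. The article does not mention net monetary benefit and gives no rule for negative ratios.

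**The concern.** A bootstrap interval, BCa included, is built from the sorted replicates. That works only if a larger value always means a worse result (or always a better one). A ratio of cost difference to effect difference has this property only under restrictions, such as when every replicate is dearer and better. Below zero it fails twice. The same negative value can mean that ACT wins on both cost and effect or loses on both. Among results where ACT wins on both, a larger health gain at the same saving moves the ratio towards zero, so the better result sorts as the worse one.

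The ICER is the only result named before the sentence that promises 95% intervals, so the natural reading is that the intervals belong to the ratios. The section intends the cost-utility result for policy making and for a guideline. At stake is whether the numerical uncertainty given for the primary economic outcomes can be read at all if costs turn out similar or lower with ACT guidance.

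**Working it through.** **The trial's own figures.** The economic section has no sample size or ratio to reproduce, so the clinical sample size sets the scale. For 19% against 11%, two-sided 5%, 80% power:

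- Uncorrected n = [1.96 x sqrt(2 x 0.15 x 0.85) + 0.8416 x sqrt(0.19 x 0.81 + 0.11 x 0.89)]^2 / 0.08^2 = 312 per group; with the continuity correction 337, as stated.
- 674 / 0.9 = 749, against 750 stated, or 375 per arm.
- Largest expected QALY gain: (0.76 - 0.73) x 0.5 year = 0.015.

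**Ordering of the ratio (arithmetic only).**

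| Cost difference (euro) | QALY difference | Ratio |
|---|---|---|
| -1,000 | +0.015 | -66,667 |
| -1,000 | +0.030 | -33,333 |
| +1,000 | -0.015 | -66,667 |

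Rows 1 and 3 are opposite conclusions with the same ratio. Row 2 is better than row 1 but sorts as worse.

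**How often replicates fall there.** Assumptions not in the protocol: QALY SD 0.08-0.16, cost SD 10,000-20,000 euro, cost and QALY independent, 375 per arm.

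- SE = SD x sqrt(2/375), so SE(QALY) = 0.0058-0.0117 and SE(cost) = 730-1,461 euro.
- P(QALY difference > 0) = Phi(0.015/SE) = Phi(2.57) to Phi(1.28) = 0.995 to 0.900.
- Zero cost difference: cheaper and better = 0.5 x 0.995 to 0.5 x 0.900 = 50% to 45%.
- Saving of 1,000 euro: P(cheaper) = Phi(1.37) to Phi(0.68) = 0.915 to 0.753; cheaper and better = 0.915 x 0.995 to 0.753 x 0.900 = 91% to 68%.
- Extra cost of 500 euro: cheaper and better = 22-36%.
- At zero cost difference, replicates that are dearer and worse make up 0.5-10% of the negative ratios.

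Simulating the ratio at the 1,000 euro saving gives percentile 95% limits from about -320,000 to +37,000 euro per QALY (smallest SDs) to about -940,000 to +760,000 (largest SDs; these tails move by a few per cent between runs).

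**BCa limits, as the plan specifies.** A separate set of assumptions: 337 per arm, correlation -0.3, 5,000 replicates, net benefit valued at 20,000 euro per QALY.

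| Cost difference | Cost SD | QALY SD | BCa 95% limits of the ratio | Net benefit 95% limits | P(net benefit > 0) |
|---|---|---|---|---|---|
| -1,000 | 8,000 | 0.08 | -240,173 to 22,695 | -12 to 2,608 | 0.97 |
| -1,000 | 15,000 | 0.12 | -619,334 to 299,330 | -1,064 to 3,726 | 0.85 |
| -2,000 | 8,000 | 0.12 | -1,396,455 to 156,899 | 913 to 3,642 | 0.999 |

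In the last row the decision is almost certain, yet the ratio's interval spans zero and more than 1.5 million euro per QALY. In every QALY scenario run, larger gains within the cheaper-and-better quadrant went with less negative ratios (rank correlation 0.23 to 0.81).

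**Prevented complications.** If these follow the 8-point difference, SE = sqrt[(0.19 x 0.81 + 0.11 x 0.89)/375] = 0.026 and z = 3.1, so about 0.1% of replicates have a negative effect. The sign of the ratio then nearly always separates cheaper from dearer, and only the order among negative values fails. With an assumed 1,000 euro saving and cost SD 12,000, the BCa limits (337 per arm) are -44,253 to 14,357.

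**The case against.** The strongest reply is that the uncertainty is already measured properly. The sentence that promises confidence intervals goes on to promise planes and acceptability curves. The plane shows all four quadrants, and the curve gives the probability of positive net benefit at each willingness-to-pay value. This stands: nobody should conclude that the plan leaves the joint uncertainty unmeasured. It does not rescue the interval, which would still be the number printed beside the primary economic outcomes.

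A reader might also infer that the trial expects ACT guidance to be both cheaper and better, so that a negative ratio is its own expected result. The documents do not support that. Only the benefit is stated. An economic benefit can mean acceptable cost-effectiveness, and fewer re-operations support lower costs only indirectly. The point does not need the inference, because replicates leave the dearer-and-better quadrant in quantity at zero and at modestly higher cost.

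The results that carry intervals could also be the cost and effect differences. That is possible; the text would then be ambiguous about its primary economic outcomes, and the same edit settles it.

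Finally, this is a condensed article, and willingness-to-pay values or a dominance convention may stand in a fuller economic plan. Their absence is not the point. The point is the stated pairing of ratio and interval.

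**Conclusion.** The concern holds in a limited form. On the natural reading, the plan attaches BCa 95% intervals to ICERs, and those intervals cannot be interpreted when replicates spread outside the dearer-and-better quadrant. With at most 0.015 QALY expected, that is likely at any true cost difference near zero or below.

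It is serious for cost per QALY. For cost per prevented complication it is milder: only the order of negative ratios is at fault, and calling both intervals equally unusable would go too far. The 0.015 QALY and the 8 points come from the protocol. All cost differences, SDs, correlations and the 20,000 euro threshold are assumptions, so the shares and limits are illustrations. The ordering fault itself needs none of them. The clinical endpoints, sample size and data collection are unaffected.

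**What to change.** In the cost-effectiveness section, attach the bootstrap 95% intervals to:

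- the incremental cost;
- the incremental QALYs;
- the complications prevented;
- the incremental net monetary benefit at willingness-to-pay values stated in advance.

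Report the ICER as a point estimate, and state dominance where one arm is both cheaper and better. Attach no interval to the ICER when replicates spread outside the dearer-and-better quadrant. Keep the planes and acceptability curves.

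The cost is wording only: the same replicates serve and no further data are needed. The one small downside is that the willingness-to-pay values must be named beforehand.

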### Cost analysis

Medical costs, patient costs, and productivity losses will be included in the evaluation. The medical costs cover the costs of surgery and related complications, anesthesia, theater, perioperative materials, inpatient stay at the ICU, and the wards and medications. The patient costs include out-of-the-pocket expenses like over-the-counter medication and health care-related travel costs. Productivity losses are costs resulting from being absent and decreased productivity during work. Hospital health care utilization will be retrieved from CRFs and hospital information systems. Data on out-of-hospital health care will be gathered with the iMTA Medical Consumption Questionnaire (iMCQ) adjusted to the study setting. The productivity losses will be documented with the iMTA Productivity Cost Questionnaire (iPCQ). Questions on out-of-pocket expenses will be added to these patient questionnaires. Costs will be price indexed based on consumer price indices (CPI).

Costs will be calculated for individual patients as the product sum of the resource use and the respective unit costs. The iMCQ questionnaire will be sent 13 and 26 weeks after surgery, and the iPCQ only 26 weeks after surgery.

